## 1.2 Aims

The objective of the study is to investigate whether a package of services at primary care level will adequately meet the needs of vertically HIV-infected children and adolescents, or alternatively whether further decentralisation to provide community-level HIV testing and/or treatment support is required.

Specific aims are:

1. To investigate the impact of treatment support provided by lay volunteers to households with one or more HIV-infected children aged 6-15 years on adherence and retention into HIV care.
2. To investigate the effectiveness of routine facility-based HIV testing and counselling in reducing rates of undiagnosed HIV infection among children aged 6-15 years in the community, over a relatively short period of time.
3. To assess the effect of ART on lung function and growth in HIV-infected children aged 6-15 years.

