## 1.3 Methodology

All children aged 6-15 years attending for acute care at primary health care clinics (PHC) in seven high-density suburbs of southwest Harare will be offered routine HIV counselling and testing during a two year period. The effectiveness of PHC-based routine PITC in providing high coverage of HIV diagnosis will be assessed through a prevalence survey for undiagnosed HIV infection in the 8-17 year age-group in the suburbs served by the PHCs. The seven PHCs will also provide decentralised HIV care, including antiretroviral therapy (ART) initiation.

Children who test HIV-positive through PITC at the PHCs will be recruited into an individual randomised trial of a voluntary lay worker (VLW)-delivered intervention to support households of HIV-infected children aged 6-15 years. Participants will be randomly allocated to either a) primary care based HIV care or b) primary care-based HIV care plus treatment support provided by VLWs, aim, aiming for equal number of control and intervention participants in each clinic. The intervention will be delivered over a eighteen month year period, the main outcomes being adherence to ART, and retention in care.

Children receiving HIV care at the PHCs including those recruited into the trial will be recruited into a clinical cohort study. Data from routine clinic visit (including height, weight, clinical symptoms, incident clinical events and adherence) will be collected. In addition, detailed growth monitoring, lung function testing and a psychosocial assessment (i.e. schooling, guardianship, and disclosure) will be carried out at pre-defined intervals. The rate of lung function decline and rates of pubertal development and growth will be compared by ART status, to investigate whether current ART initiation guidelines can prevent or delay progression of chronic lung disease and/or growth failure.

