## 1.4 Trial outcomes

Comparison between intervention and control arms of:

- Proportion of children on ART with treatment failure defined as an HIV-1 viral load >400copies/ml at 12 months after starting ART or death in the first year of ART
- Proportion of children who miss two or more *routine* appointments by the end of two years of follow-up. This outcome has been chosen as studies have consistently shown that missed appointments are associated with worse health outcomes and poorer adherence to treatment.4

Other comparisons between arms will include:

1. all-cause mortality
2. numbers of and time to first hospital admission
3. numbers of unscheduled visits to PHC
4. proportion of children who have an average adherence rate <80% 12 months after starting ART
5. proportion of children who change to 2nd line ART as a result of treatment failure

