### 3.4.2 Individual-randomised trial of household support

The unit of randomization will be an individual attending each clinic, and not households, however, the trial outcomes will be evaluated at the level of the clinic to cater for any clustering at clinic (suburb) level. The main differences between the two arms will be:

- Proportion on ART with treatment failure defined as an HIV-1 viral load >400copies/ml at 12 months after starting ART or death in the first year of ART
- Proportion who miss two or more *routine* appointments by the end of two years of follow-up

Other comparisons between arms will include:

1. all-cause mortality
2. numbers of and time to first hospital admission (defined as stay in hospital for ≥24 hours)
3. numbers of additional attendances (over and above routine follow-up) to PHC
4. proportion of children who have an average adherence rate <80% 12 months after starting ART
5. proportion of children who change to 2nd line ART as defined by National Guidelines (due to reasons not related to toxicity, side-effects or starting TB treatment)

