## 11.2 Sample size estimates

### 11.2.1 Individual-randomised trial

A sample of 175 children with newly diagnosed HIV per arm provides 80% power to detect a 45% reduction in proportion of children who miss ≥2 routine appointments in the follow up period in the intervention arm relative to the standard of care arm, given the most likely scenario of 30% missing in the control arm 4, 86, and allow 10% loss to follow-up, assuming a baseline HIV prevalence of 1.8%. The study also has 83% power to detect a 40% difference in proportions who miss ≥2 appointments, assuming that rates in the unexposed arm is 40%.

Studies have shown virological failure rates of 30-70% in older children. 1, 87-88 Assuming that at least 70% of the 175 children per arm with newly diagnosed HIV start ART, we expect 123 children per arm to be on ART. If the treatment failure/death rate among controls is 50%, the study will have 87% power to detect a 40% reduction in this rate. Given that our retention rate into the trial is better than expected, 350 participants will therefore provide adequate power to detect the difference in retention in care between the trial arms, even with the lower sample size.

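### Adherence is a main outcome in 1.3 but an 'other comparison' in 1.4 and 3.4.2, and neither of the two powered outcomes is named as the one that decides the trial

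*Protocol*

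**What the plan says.** - **Protocol 1.2, Aim 1:** the lay-worker support is to be evaluated for its impact "on adherence and retention into HIV care".
- **Protocol 1.3:** the same pair is used, "the main outcomes being adherence to ART, and retention in care".
- **Protocol 1.4:** the list begins with "Proportion of children on ART with treatment failure defined as an HIV-1 viral load >400copies/ml at 12 months after starting ART"; children who die during their first treatment year also count as failures. Next comes missing two or more routine appointments. Adherence comes fourth under the other comparisons: "proportion of children who have an average adherence rate <80% 12 months after starting ART".
- **Protocol 3.4.2:** "The main differences between the two arms will be" introduces the same two outcomes as 1.4, with adherence again fourth among the others.
- **Protocol 11.2.1:** 175 per arm "provides 80% power to detect a 45% reduction" in missed appointments. Failure/death is then powered separately: "If the treatment failure/death rate among controls is 50%, the study will have 87% power to detect a 40% reduction in this rate". The section closes with "350 participants will therefore provide adequate power to detect the difference in retention in care between the trial arms".

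The protocol gives no significance level or sidedness. It does not rank the two outcomes, and it does not say whether one or both must succeed.

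**The concern.** Adherence cannot be both a main outcome and an other comparison. Behind that wording conflict lies a larger gap: the protocol does not say which result decides whether household support works.

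The two listed outcomes differ in kind. Section 6 has the lay workers remind caregivers of appointments, so missed appointments is a process measure on which the intervention acts directly. Treatment failure/death is a health outcome, measured only in the children who start ART (assumed 70% in 11.2.1). The two can disagree, and the protocol does not say what would then be concluded. The outcome that carries the headline could be chosen after the results are known.

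**Working it through.** **1. The lists side by side**

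| Section | Main | Adherence |
|---|---|---|
| 1.2 (Aim 1), 1.3 | adherence; retention | main |
| 1.4, 3.4.2 | failure/death; missed appointments | other comparison |
| 11.2.1 | both of the latter powered; closing sentence on retention only | not powered |

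Retention corresponds to missed appointments in every section. The conflict is therefore adherence against treatment failure/death.

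**2. Reproducing the stated powers**

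Inputs from 11.2.1:
- Missed appointments: 175 per arm with 10% loss gives 175 × 0.9 = 157.5 evaluable. The scenarios are 30% v 30% × 0.55 = 16.5%, and 40% v 40% × 0.60 = 24%.
- Failure/death: 123 per arm on ART, 50% v 50% × 0.60 = 30%.

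Formula: power = Φ[(d − z·s0)/s1], where
- d = |p1 − p2|, reduced by 1/n with the continuity correction;
- s0 = √(2p̄(1 − p̄)/n);
- s1 = √((p1(1 − p1) + p2(1 − p2))/n).

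Example, 30% v 16.5%: d = 0.135, s0 = 0.0476, s1 = 0.0470. Power = Φ[(0.135 − 1.96 × 0.0476)/0.0470] = Φ(0.888) = 81.3%.

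| Contrast | Stated | Two-sided 5% | Two-sided 5%, corrected | Two-sided 2.5% | One-sided 5% |
|---|---|---|---|---|---|
| 30% v 16.5% | 80% | 81.3% | 77.4% | 72.7% | 88.6% |
| 40% v 24% | 83% | 86.4% | 83.6% | 79.2% | 92.2% |
| 50% v 30% | 87% | 89.8% | 87.2% | 83.7% | 94.4% |

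(The last two columns are uncorrected.) No single variant matches all three figures: 80% is nearest the uncorrected formula, while 83% and 87% match the corrected one. Two-sided 5% for each outcome is the only level tried that comes within 2 points of every stated figure. A split to 2.5%, or a one-sided 5% test, does not.

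**3. Error rate if either outcome suffices**

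With two independent two-sided 5% tests, the chance of at least one false significant result is 1 − 0.95² = 9.75%. In the favourable direction only, it is 1 − 0.975² = 4.94%, to be compared with 2.5% for one test. For correlated tests the bivariate normal gives:

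| Correlation (assumed) | Either direction | Favouring support |
|---|---|---|
| 0 | 9.8% | 4.9% |
| 0.5 | 9.1% | 4.5% |
| 0.75 | 8.1% | 4.0% |

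If both outcomes must be significant, the error cannot exceed 5%.

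**4. How often the outcomes would disagree**

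Suppose both design effects are true (30% v 16.5%, 50% v 30%) and each is tested at 5% without correction. Exactly one test is then significant in 25% of trials at correlation 0, 19% at 0.5 and 14% at 0.75.

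**5. Power under Holm at overall two-sided 5%** (range over correlation 0 to 0.75; simulation where both effects exist)

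| Outcome | Both effects exist | Corrected | Only that effect exists | Corrected |
|---|---|---|---|---|
| Missed appointments, 30% v 16.5% | 79-80% | 75-76% | 73% | 68% |
| Failure/death, 50% v 30% | 86-88% | 83-85% | 84% | 80% |

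**The case against.** **Multiplicity rules usually sit in the SAP, which is not shown.** This stands as far as it goes: a missing Holm rule or alpha split in the protocol is not itself a fault. But an analysis plan cannot make two contradictory protocol lists agree, and which outcome decides the trial is a design matter.

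**The conflict is narrow.** This stands in part. Treatment failure and missed appointments appear together in 1.4, Figure 1.1, 3.4.2, 9.2.2 and 11.2.1, and retention is common to all sections. Section 1.3 may be using adherence loosely for viral suppression. The text does not say so, however, and section 7 assesses adherence by self or caregiver report.

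**A reader might infer a 9-10% chance of a false claim for lay-worker support.** The documents do not support that. The 8-10% figure counts false results in both directions, including those suggesting harm. In the favourable direction it is about 4-5%, against 2.5% for one test. Both figures also assume that a win on either outcome is enough, which the protocol nowhere says. If each outcome is reported as its own separate claim, each test keeps its 5%.

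**The 5% level is inferred.** This stands. It is the reading that best fits the stated powers, not a stated value.

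**Conclusion.** The protocol contradicts itself on whether adherence is a main outcome. It lists and powers two outcomes without saying which one, or whether both, decides the trial. That holds on the text alone.

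The size of the consequence is conditional. It rests on an inferred two-sided 5% per outcome, on success on either being sufficient, and on an assumed correlation of 0 to 0.75. Under those assumptions the error is about 8-10% in either direction instead of 5%, or about 4-5% in favour of support instead of 2.5%. It is close to double in relative terms at low correlation and smaller as correlation rises. If both outcomes are required, there is no inflation.

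This should be corrected, but it does not undermine the design or the sample size.

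**What to change.** Use one list of main outcomes in 1.3, 1.4, 3.4.2 and 11.2.1, with adherence secondary throughout, and align Aim 1 with it. Then choose one of the following.

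1. **Single primary.** Name either missed appointments or treatment failure/death as primary and make the other secondary. The stated power of the chosen outcome is unchanged. The cost is that only one outcome carries the confirmatory claim.
2. **Co-primary under Holm at overall two-sided 5%.** Test the smaller p-value at 2.5% and, only if it passes, the other at 5%. Claim an effect only for the outcome(s) rejected. Restate power in 11.2.1 from step 5 of the working, saying whether the continuity correction is used. The cost is lower stated power, most of all if only one effect exists.

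A fixed sequence starting with missed appointments would also control the error. With both effects present, it would cut power for failure/death to about 73-78% uncorrected or 67-74% corrected, against the stated 87%, so it is not free.

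In either case, state alpha and sidedness in 11.2.1. Also align 9.2.2, which counts participants with more than two missed appointments where 1.4 and 3.4.2 count two or more. These are changes of wording and of the power statement. They need no extra participants or data.

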**Follow-up of all children:**

- Missed clinic visits
- Death- interview family + hand-held records for cause of death
- Lung function, height, weight and head circumference, pubertal stage
- Adherence: self-report, pill-count
- School attendance and guardianship
- ART failure: HIV viral load and CD4 count
- Hospital admission and new diagnoses (hand-held records for cause)
- Identification of elite controllers

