## 4.5 Participant selection, inclusion and exclusion criteria

The inclusion criteria for participation in the trial will be:

- age between 6 years (day of their 6th birthday and older) and 15 years (a day before their 16th birthday)
- test HIV-positive following PITC in the PHC
- willing to have their HIV care at the PHC
- usual residence in the study suburb where the PHC is located
- informed consent by parent and assent from child to participate

The exclusion criteria for participation in the trial will be:

- age <6 years or ≥16 years
- usual residence outside the study suburb where the PHC is located
- previously tested HIV+ positive and receiving care (clinical or psychosocial)
- not planning to access HIV care at the PHC

All participants enrolled into the trial will automatically be offered enrolment into the cohort study. Additionally, any children aged 6-15 years who test HIV-positive following PITC after enrolment for the trial is completed, will also be approached for recruitment into the clinical cohort study.

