**Table 7.2 Follow-up schedule for cohort participants who start ART**

|  |  | **Week** | | | | | | | | | | |
| --- | --- | --- | --- | --- | --- | --- | --- | --- | --- | --- | --- | --- |
| **0** | **2** | **4** | **6** | **8** | **12** | **24** | **36** | **48** | **60** | **72** |  |
| Start ART |  |  |  |  |  |  |  |  |  |  |  |  |
| Nurse visit/collect medication1 |  |  |  |  |  |  |  |  |  |  |  |  |
| Weight/Height |  |  |  |  |  |  |  |  |  |  |  |  |
| HC, MUAC2 |  |  |  |  |  |  |  |  |  |  |  |  |
| Lung function testing |  |  |  |  |  |  |  |  |  |  |  |  |
| T-cell subsets |  |  |  |  |  |  |  |  |  |  |  |  |
| HIV-1 viral load *(1 year post-ART)* |  |  |  |  |  |  |  |  |  |  |  |  |
| Blood sample store3 |  |  |  |  |  |  |  |  |  |  |  |  |
| Psychosocial assessment4 |  |  |  |  |  |  |  |  |  |  |  |  |
| Pubertal Staging5 |  |  |  |  |  |  |  |  |  |  |  |  |
| Adherence assessment |  |  |  |  |  |  |  |  |  |  |  |  |
| Referral for TB investigations (if TB symptoms)6 |  |  |  |  |  |  |  |  |  |  |  |  |

1Clinical & toxicity symptom checklist, hospitalisation, new diagnoses

2HC-head circumference; MUAC- mid-upper arm circumference;

3Blood sample also taken at recruitment

4Knowledge of diagnosis, disclosure to others, schooling, guardianship, family HIV test

5For children aged 9 years or older

6Sputum (expectorated or induced), CXR, stool, urine will be collected as part of a collaborative study to be conducted by [name] (see Appendix 18.10)

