### 9.2.2 Trial

The cumulative total number of children aged 6-15 years offered PITC who test HIV-positive and are recruited into the study under the trial arms will be determined.

The following data on the children who test HIV positive through PITC will be collected on study forms:

- Recruited or not recruited into the study
- Study arm recruited
- Routine clinic appointment dates on the clinic card and the actual visit date
- Any additional study visits
- On ART or not started
- Date started on ART
- CD4 count
- Viral Load post 12months ART
- On first vs second-line ART
- Pill count
- Adherence assessment result

Further, HIV-positive participants in each arm started on ART and date started will be used to determine if the participant has been on ART for a period of one year or more. The cumulative total number of participants who have been on ART for a period of ≥1 year will be determined.

A field will be generated which calculates the number of days between the routine appointment date and the actual routine visit date. If the difference is more than 7 days, an appointment will be classified as missed. The cumulative number of missed appointments for each participant will be calculated; the proportion of participants with more than two missed appointments will then be calculated for each arm.

Another ART outcome field will be generated which determines if the viral load is >400 copies/ml or if the participant has died within a period of one year on ART. If this is true, the ART outcome will be classified failure otherwise it will classified as success or unknown if the participant is lost to follow-up.

If the patient has not attended for an appointment for a period of >6 months, they will be followed up to ascertain the cause of this (death/move out of area/default /other). If alive and still in the area, cause of default will be determined as well as relevant clinical information. If agreeable the current viral load will be determined and the participant encouraged to re-attend for HIV care.

If the participant has died and the family is still in the area, the date of death will be recorded and a brief verbal autopsy conducted to ascertain the cause of death.

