### 9.2.4 Cohort Study

The following data will be recorded for participants enrolled in the cohort study:

- ART status
- CD4 count
- Weight, height, MUAC, HC, pubertal stage
- FEV1, FVC and FEV1: FVC
- Incident opportunistic infections, including TB
- Hospitalisations
- Deaths
- Side-effects of ART
- Adherence
- School attendance rates
- Disclosure
- Type or guardianship

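### Hospital admission is compared between arms, but its described capture depends on attendance, which the intervention aims to raise, so control-arm admissions may be under-recorded

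*Protocol*

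**What the plan says.** Section 3.4.2 lists "numbers of and time to first hospital admission (defined as stay in hospital for ≥24 hours") among the other comparisons between arms, and section 1.4 lists the same outcome without the 24-hour definition.

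Section 9.2.2 sets out the trial data under "The following data on the children who test HIV positive through PITC will be collected on study forms". Its items are recruitment and arm, appointment and actual visit dates, additional visits, ART status and start date, CD4 count, viral load, ART line, pill count and adherence. Admission is not among them. Section 9.2.4, introduced by "The following data will be recorded for participants enrolled in the cohort study", does include "Hospitalisations". The footnotes to Tables 7.1 and 7.2 place the question in the nurse visit (in Table 7.2, "toxicity symptom checklist, hospitalisation, new diagnoses"). None of these places mentions an admission date or length of stay.

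Three other places bear on the point:
- Figure 1.1, under follow-up of all children, lists "Hospital admission and new diagnoses (hand-held records for cause").
- Section 4.5 states: "All participants enrolled into the trial will automatically be offered enrolment into the cohort study". Entry to the cohort is therefore offered, not assured.
- Section 9.2.2 has children traced after more than 6 months without attendance. If the child is alive and still in the area, the reason for default and unspecified clinical details are obtained. If the child has died and the family is still in the area, the date of death is recorded and a brief verbal autopsy establishes the cause. Neither contact names admissions.

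**The concern.** The number of admissions and the time to the first one can be compared fairly only if an admission is equally likely to be recorded in each arm. The capture described here runs through clinic attendance, which is itself a main outcome and the thing the lay-worker support is meant to improve. No source independent of attendance, such as hospital registers, is named. Lay workers also visit intervention homes and follow up with clinic staff (sections 6 and 6.2), a channel of information that controls lack.

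An admission after a child's last attended visit, including one that ends in death, is recorded only if tracing happens to pick it up. If more control children stop attending, more control admissions go unrecorded. The recorded ratio then moves against the intervention, and part of any real reduction in morbidity is hidden. Analysis cannot recover admissions that were never collected.

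**Working it through.** **Inputs from the Protocol (section 11.2.1).** 175 children per arm; 30% of controls missing two or more appointments; a 45% relative reduction, so 0.30 × 0.55 = 16.5% in the intervention arm; 10% loss to follow-up. No figure is given for admissions.

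**The plan's own figure.** Evaluable children per arm are 175 × 0.9 = 157.5. With two-sided alpha 0.05 (assumed; not stated) and mean proportion 0.2325:
- null standard error = √(2 × 0.2325 × 0.7675 / 157.5) = 0.0476
- alternative standard error = √((0.30 × 0.70 + 0.165 × 0.835) / 157.5) = 0.0470
- power = Φ((0.135 − 1.96 × 0.0476) / 0.0470) = Φ(0.887) = 81.3%

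This agrees with the stated 80%, so the attendance contrast can be used as the plan's own.

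**Effect on the admission ratio.** Let q be the proportion of an arm whose admissions are at risk of being missed, and c the share of those children's admissions never recorded. Assume the same true admission rate in these children as in the others. Capture in an arm is 1 − qc, so

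recorded ratio = true ratio × (1 − q_int × c) / (1 − q_con × c).

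The Protocol gives no value for c. The range below is an assumption.

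*Narrow case: loss only in children who never return.* Take the planned 10% loss as the control rate and apply the same 45% reduction, giving 5.5%. Both steps are assumptions; the Protocol gives no loss rate by arm. With equal true rates:
- c = 0.50: 0.9725 / 0.950 = 1.02
- c = 0.75: 0.95875 / 0.925 = 1.04

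*Wide case: loss in all children missing two or more appointments, 30% v 16.5%.* With equal true rates:
- c = 0.50: 0.9175 / 0.850 = 1.08
- c = 0.75: 0.87625 / 0.775 = 1.13

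**If the intervention truly lowers admissions.** A true ratio of 0.80 in the wide case is recorded as 0.80 × 1.079 = 0.86 (c = 0.50) or 0.80 × 1.131 = 0.90 (c = 0.75). In the narrow case it is recorded as 0.82 to 0.83. In the wide case the recorded ratio exceeds 1 only if the true ratio is above 1/1.079 = 0.93 (c = 0.50) or 1/1.131 = 0.88 (c = 0.75).

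**The case against.** A reader might infer that admissions are captured only at attended cohort visits, and that children who decline the cohort have no admission data. The Protocol does not support that. Figure 1.1 lists admission for all children. Section 5.2 has incident clinical events recorded at each follow-up visit in routine HIV care. Section 7.3 lists what is not done for children outside the cohort, and the hospitalisation question is not on that list. The bullets in 9.2.2 are also not exhaustive: they omit death, which the same section handles further down. The trial SOPs and study forms are held in separate appendices, so whether the forms lack an admission field cannot be known.

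A reader might also infer that the better-attending arm will appear to have more admissions. That would need little or no true benefit. As shown above, a true ratio of 0.80 still favours the intervention in every case worked.

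The wide case probably overstates the loss. Under section 9.1 an appointment counts as missed when attendance is more than 7 days late, and section 7.2 rebooks it at the next available date. A child who misses two of the ten visits scheduled in Table 7.1 can therefore still report an earlier admission at the next one. Loss is firm mainly in children who never return, and admissions before they stop attending are already recorded.

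All of this stands, and it reduces the size of the problem without removing it. Figure 1.1 names hand-held records only for cause and gives no route for children who stop attending. Section 5.2 works only through attended visits, and tracing is late, conditional and silent on admissions.

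**Conclusion.** The comparison is open to differential ascertainment. The Protocol declares an admission outcome, leaves it out of the trial data list, and describes a capture route that depends on attendance. The likely direction is a higher recorded intervention/control ratio, so a real benefit would more probably be attenuated than reversed.

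The size is unknown. The narrow case (1.02 to 1.04) is the better-grounded of the two and the wide case (1.08 to 1.13) is an upper illustration. Both rest on an assumed half to three quarters of admissions unrecorded in the affected children, on equal true admission rates in those children and the rest, and on an attendance effect as large as planned. If poor attenders are admitted more often than others, the factor would be larger; if later visits or tracing recover most admissions, it would be smaller.

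This is one of five other comparisons and carries no power claim, so the point is modest. It should be settled before data collection, because it cannot be repaired at analysis.

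**What to change.** Add the date and length of stay of each admission to the section 9.2.2 data for every randomised child, whether or not in the cohort. Ask it on the same form in both arms:
- at each attended visit, covering the time since the last visit;
- at the tracing contact already planned after more than 6 months' absence;
- in the verbal autopsy already planned after a death.

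Use hand-held records where available. Do not use lay-worker reports as a source, since only one arm has them.

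Report admissions per child-time with known admission status, and show the unascertained time by arm so that a reader can judge the imbalance. State plainly that censoring time to first admission at the last ascertained date does not remove informative dropout; fuller ascertainment at tracing and after death is what reduces it.

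The cost is a few form items and a person-time denominator, with no extra visits.
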